### **6.1.2 Methods for Pre-operative Evaluation of Measurable Disease**

All measurements should be taken and recorded in metric notation using a ruler or calipers. All baseline evaluations should be performed as closely as possible to the beginning of treatment and not more than Response Criteria on MRI. Response assessment to stereotactic radiotherapy will be performed using contrast-enhanced dynamic breast MRI (DCE-MRI) imaging.

Recommended MRI technique: (may not be possible for all MRI's as some may be done at outside facilities)

Recommended MRI studies will be performed with the patients lying prone in a scanner using a dedicated multi-channel breast array coil (MRI Devices Corporation, Pewaukee, WI). The breast MRI protocol is attached and will comprise pre-and post contrast dynamic 3-dimensional fast spoiled-gradient echo image sets, as well as diffusion weighted image series (DWI). Images will be obtained during and following rapid intravenous bolus infusion of gadolinium contrast at a rate of 3 mL/sec with a power injector (Spectris Solaris MR Injector; Medrad, Warrendale, PA) with delayed postcontrast 3-dimensional fast spoiled-gradient echo images with fat suppression in both axial and sagittal planes obtained.

#### Imaging response assessment

i. The precontrast dynamic image set will be subtracted from the postcontrast sets, and time-intensity curves will be obtained from contrast-enhanced lesions with a hand-drawn region of interest (ROI) encompassing the lesion, with a

minimum ROI size of  $3 \times 3$  pixels. The time-intensity curve demonstrating maximal change will be selected as representative for a lesion to perform pharmacokinetic analysis as needed. Further same measurements will be performed from peritumoral stroma (within 2 cm of the tumor margins) to measure the radiation effect on stroma.

ii. *Volume changes*: Tumor enhancement volume (signal enhancement ratio) prior to and after therapy will be derived using dedicated software (DynaCAD, Philips) and post-therapy enhancement volume change (%) will be computed. In addition, percentage change in tumor size will be assessed using the following formula for ellipsoidal or spherical volume derived from mid-dynamic sequence subtraction series:

$$V (\text{cm}^3) = (4/3 \pi) \times \text{length}/2 \times \text{width}/2 \times \text{height}/2$$

iii. *Pharmacokinetic Analysis*: In the subgroup of patients who undergo baseline and follow up MRI imaging in our institution, A 3-parameter, 2-compartment general kinetic model will be used to derive PK parameters (Ktrans, kep, and ve). A Weimann arterial input function will be used as the population model. Parameters Ktrans (min), kep (min), and ve (unitless) will be computed from the change in signal intensity data, which is converted to gadolinium concentration pixel-by-pixel within a defined ROI. The mean values of these parameters will be compared pre-and post therapy.

iv. *Kinetic changes*: Model-independent analysis will be performed by directly measuring of the slopes of signal intensity wash-in and wash-out curves (maximum slope, sec), contrast enhancement ratio, and IAUC90.

v. *Diffusion Weighted Imaging when performed- changes* within the tumor, both DWI signal and ADC values will be measured and compared to pre-treatment values as applied.

#### MRI Analysis

A univariate logistic regression model will be used to estimate the odds of response (complete or partial), estimating the odds ratio for each potential imaging parameter with a 95% confidence interval. Logistic regression analysis will be performed to assess the relationship between imaging response parameters (volume, kinetic and DWI) and pathologic (complete or partial) response."

### **6.1.3 Progression-Free Survival**

Progression-free survival (PFS) is defined as the duration of time from start of treatment to time of progression.

## **6.2 Criteria for Cosmetic Outcome Photography**

Photographs of both breasts will be taken and cosmesis will be graded by the patient, and the radiation oncologist, at twelve months from the start of therapy and at yearly intervals thereafter for up to 5 years after treatment. In addition, an independent panel established at University of Texas Southwestern Medical Center will evaluate cosmesis at the end of study based on photography. See Appendix III and IV for physician and patient cosmesis forms.

Excellent: When compared to the untreated breast, there is minimal or no difference in the sizes, shape, or texture of the treated breast. There may be mild thickening or scar tissue within the breast or skin, but not enough to change the appearance.

Good: There is mild asymmetry in the size or shape of the treated breast as compared to the normal breast. The thickening or scar tissue within the breast causes only mild change in the shape.

Fair: There is obvious difference in the size and shape of the treated breast. This change involves  $\frac{1}{4}$  or less of the breast.

Poor: Marked change in the appearance of the treated breast involving more than  $\frac{1}{4}$  of breast tissue

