### 2.2 Secondary Objectives

- 2.2.1 Local Control
- 2.2.2 Acute Toxicity (90 Days)
- 2.2.3 Late Toxicity (24 months)
- 2.2.4 Rates of Surgical Morbidity
- 2.2.5 Pathologic Complete Response Rates
- 2.2.6 Patient and Physician Cosmesis Outcomes
- 2.2.7 Distant Disease-Free Survival

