#### **4.5 Duration of Follow Up**

Subjects will be followed for **5 years**. Subjects removed from treatment for unacceptable adverse events will be followed until resolution or stabilization of the adverse event. Patients will be followed 1, 3, 6, 12, 24, and 36 months after radiation. See [Section 5.4](#) Time and Events Table for follow-up visit windows.

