### **5.1.15 Patient and Physician Cosmesis Forms (Appendix III and IV)**

Both patients and physicians will fill out patient cosmesis forms at baseline and per Section 5.4 time and events table.

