**5.2.9 36 months after Radiation**

- History and Physical Exam
- Breast Assessment/Examination
- Toxicity/Adverse event evaluation
- Breast Imaging
- Breast Digital Picture (see section 5.1.12 for details)
- Patient and Physician Cosmesis forms

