| Breast Digital Picture                            | X   |                          |                                |                 |                                    |                                 |                                 |                                 |                                  | X                                |
| Patient Cosmesis Forms (Appendix III)             | X  |                          |                                |                 |                                    |                                 |                                 |                                 |                                  | X                                |
| Physician Cosmesis Forms (Appendix IV)            | X  |                          |                                |                 |                                    |                                 |                                 |                                 |                                  | X                                |
| Optional Blood Samples                            | X   |                          | X                              |                 | X                                  |                                 |                                 |                                 |                                  |                                  |
| Tumor Sample                                      | X   |                          |                                | X               |                                    |                                 |                                 |                                 |                                  |                                  |
| Optional Tumor Sample                             | X   | X            |                                |                 |                                    |                                 |                                 |                                 |                                  |                                  |

1 Follow-ups can be done within +/- 21 days of time points above and can be done via telehealth

2 Follow-ups can be done within +/- 60 days of time points above and can be done via telehealth

3 To be completed within 30 days prior to radiation

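### Section 6.2 plans yearly cosmesis grading from 12 months for up to 5 years, but the schedule collects it only before radiation and at 36 months, the last visit

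*Protocol*

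**What the plan says.** Section 6.2 sets the timing of photographs and of patient and physician grading: "at twelve months from the start of therapy and at yearly intervals thereafter for up to 5 years after treatment". It adds an independent panel that judges cosmesis from the photographs at the end of the study.

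The operational sections say something else. Section 5.1.15 reads "Both patients and physicians will fill out patient cosmesis forms at baseline and per Section 5.4 time and events table". In that table, the rows for the digital picture, the patient form and the physician form are marked in two columns only: before radiation and 36 months after it. The visit lists agree with the table. The 36-month list (5.2.9) includes "Breast Digital Picture (see section 5.1.12 for details") and "Patient and Physician Cosmesis forms". The 12-month list (5.2.7) and the 24-month list (5.2.8) include a physical examination, breast examination, toxicity review and breast imaging, but no photograph and no cosmesis form.

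On the length of follow-up, section 4.5 gives 5 years and, in the same paragraph, "Patients will be followed 1, 3, 6, 12, 24, and 36 months after radiation". Section 5.3 and the table also stop at 36 months.

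Footnote 2 of the table, which covers the 12-, 24- and 36-month visits, says "Follow-ups can be done within +/- 60 days of time points above and can be done via telehealth".

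**The concern.** Sections 2.2 and 10.1 list patient and physician cosmesis as a secondary objective and endpoint. Section 4.1.10 names a worse cosmetic result, early or late, as a risk of the treatment. Section 1.2 cites a randomised trial of ten-fraction partial breast irradiation in which nurse-rated fair or poor cosmesis at five years was 32.8% against 13.4% with whole-breast treatment. The time course of cosmesis is therefore of direct interest here.

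Coordinators work from the visit lists and the table. Followed as written, these give one post-treatment assessment per patient, with no earlier value to show change and nothing at all for a patient who leaves before month 36. No analysis plan can restore photographs and forms that were never collected.

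**Working it through.** The protocol gives no figure to reproduce, so the check sets the sections side by side. Section 6.2 counts from the start of therapy and the schedule counts from radiation. Treatment is a single fraction, so the two origins coincide.

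| Month | Grading under 6.2 | Visit in 4.5, 5.3 and 5.4 | Photograph and both forms in 5.2 and 5.4 |
|---|---|---|---|
| 12 | yes | yes | no |
| 24 | yes | yes | no |
| 36 | yes | yes | yes |
| 48 | yes, within the 5-year ceiling | no | no |
| 60 | yes, within the 5-year ceiling | no | no |

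1. By month 36, section 6.2 implies 3 assessments (12, 24, 36) and the schedule provides 1.
2. By month 60, section 6.2 implies up to 5 assessments (12, 24, 36, 48, 60) and the schedule provides 1.
3. Of the 4 that are missing, 2 (months 12 and 24) have a visit but no cosmesis item, and 2 (months 48 and 60) have no visit.

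One further check concerns what a 12-month grade would measure. Sections 4.3.1 and 8.1 allow surgery from 8 to 52 weeks after radiation, so as late as day 52 × 7 = 364. Footnote 2 gives the 12-month visit a window of 60 days either side. Taking 12 months as 365 days, the visit can fall between day 365 − 60 = 305 and day 365 + 60 = 425. A 12-month grade may therefore come before surgery or shortly after it. The earliest 24-month visit is day 730 − 60 = 670, which is after the latest allowed surgery. Month 24 is thus the first yearly assessment that is post-surgical for every patient operated on within the stated period, and it is not scheduled.

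**The case against.** The best reply is that section 6.2 may be the outlier. Section 5.1.15 defers to the table, and 5.2.9, 5.3, 5.4 and the visit list in 4.5 all fit a 36-month schedule. Correcting one sentence in 6.2 would remove the contradiction. The 5 years there are also a ceiling, so 1 of 5 is the harshest count. This has force for months 48 and 60. It does not explain months 12 and 24, which 6.2 names or implies without qualification and for which visits already exist. Cutting 6.2 back to the table would make the text consistent but would leave one assessment per patient.

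The telehealth permission is optional wording. The 36-month visit lists a physical examination, imaging and a photograph, so the footnote need not be read as waiving them. What stands is a need for clarification: section 5.1.12 asks for two standardised views, and nothing says that a visit with photographs must be in person.

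A reader might infer more than the protocol supports:

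- That a definite number of patients will lack cosmesis data. The protocol gives 7 to 60 patients and no attrition rate, so no count follows.
- That a blinded review is compromised. Section 6.2 calls the panel independent and does not mention blinding.
- That "Late Toxicity (24 months") in section 2.2 contradicts the 36-month late adverse event period in 7.2.1. A 24-month endpoint can be evaluated within a 36-month collection window.
- That promised 5-year estimates cannot be delivered. Section 10.3 plans Kaplan-Meier curves without a landmark time, and 6.1.1 says all patients are followed for survival. Contact after month 36 is unscheduled, which is not the same as absent.

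**Conclusion.** The contradiction is certain, and no other text in the protocol resolves it. Section 6.2 requires cosmesis assessments that sections 5.2 and 5.4 do not collect, and the 5 years in section 4.5 have no visits behind them after month 36. Followed as scheduled, the trial obtains 1 of 3 planned post-treatment assessments by month 36, or 1 of up to 5 by month 60.

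The conclusion assumes that sites follow the visit lists and table rather than 6.2. It concerns a secondary endpoint. Dose escalation, the 90-day assessment and the primary endpoint are untouched. The point should be corrected because the loss is permanent once the 12- and 24-month visits have passed.

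**What to change.** 1. Add photographs and both cosmesis forms to the 12- and 24-month visits in 5.2.7, 5.2.8 and the 5.4 table.
2. State that visits with photographs are in person, as an exception to footnote 2.
3. Bring 4.5, 5.3, 5.4 and 6.2 to one horizon: either 36 months throughout, or scheduled annual contacts to 60 months.
4. Record for each cosmesis grade whether it was taken before or after surgery. Do not substitute a 12-month grade for a missing 36-month grade, since the two may describe the breast before and after surgery.

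The cost is two short forms and a set of photographs at each of two existing visits, plus the amendment of the table and text. If the 60-month horizon is chosen, the contacts at months 48 and 60 are an additional cost.

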### **6.3 Safety/tolerability**

Analyses will be performed for all subjects having received at least one fraction of radiation therapy. The study will use the CTCAE version 5.0 for reporting of adverse events.

[https://ctep.cancer.gov/protocolDevelopment/electronic\\_applications/ctc.htm](https://ctep.cancer.gov/protocolDevelopment/electronic_applications/ctc.htm)

## **7.0 ADVERSE EVENTS**

### **7.1 Experimental Therapy**

#### **7.1.1 Adverse Reactions**

##### Rib Fracture

The consequences of rib fracture should all be graded according to the Common Terminology Criteria For Adverse Events (CTCAE).

##### Skin

Monitored treatment related toxicity associated with skin function will include fibrosis, rash (desquamation), blistering, ulceration, and telangiectasia. The consequences of skin toxicity should all be graded according to the Common Terminology Criteria For Adverse Events (CTCAE).

##### Radiation Pneumonitis

Radiation pneumonitis is unlikely to be seen in patients treated on this protocol. Radiation pneumonitis is a subacute (weeks to months from treatment) inflammation of the end bronchioles and alveoli. Note: It is very important that a Radiation Oncologist participate in the care of the patient, as the clinical picture may be very similar to acute bacterial pneumonia, with fatigue, fever, shortness of breath, nonproductive cough, and a pulmonary infiltrate on chest x-ray.

Patients reporting symptoms as above will be promptly evaluated and treated. Mild radiation pneumonitis may be treated with nonsteroidal anti-inflammatory agents or steroid inhalers. More significant pneumonitis will be treated with systemic steroids, bronchodilators, and pulmonary toilet. Supra- and concurrent infections should be treated with antibiotics. Consideration of prophylaxis of opportunistic infections should be considered in immunocompromised patients.

Radiation pneumonitis will be graded according to its constituent effects including fever, dyspnea, chest pain, and cough according to the Common Terminology Criteria For Adverse Events (CTCAE) version 5.

Neurological (intercostal or brachial plexus nerves) or any grade 4 or 5 toxicity deemed definitely attributed to the therapy.

Other Toxicities

Other treatment related toxicity attributed to the therapy will be captured, recorded and the consequences of should all be graded according to the Common Terminology Criteria For Adverse Events (CTCAE) version 5.

**7.2 Adverse Event Monitoring**

Adverse event data collection and reporting, which are required as part of every clinical trial, are done to ensure the safety of subjects enrolled in the studies as well as those who will enroll in future studies. Adverse events are assessed in a routine manner at scheduled times during a trial. Additionally, certain adverse events must be reported in an expedited manner to allow for optimal monitoring of subject safety and care.

All subjects experiencing an adverse event, regardless of its relationship to study therapy, will be monitored until:

- the adverse event resolves or the symptoms or signs that constitute the adverse event return to baseline or is stable in the opinion of the investigator;
- there is a satisfactory explanation other than the study therapy for the changes observed; or
- death.

Note: Adverse events that occur from consent to the end of the acute adverse events reporting period as defined in section 7.2.1 will be documented. Any event that occurs during the late adverse event period as defined in section 7.2.1 and is attributed (possibly, probably, or definitely) to the agent(s) must also be documented and reported if it meets Serious Adverse Event criteria (See Section 7.3).

**7.2.1 Definitions**

An adverse event is defined as any untoward or unfavorable medical occurrence in a human research study participant, including any abnormal sign (for example, abnormal physical exam, imaging finding or clinically significant laboratory finding), symptom, clinical event, or disease, temporally associated with the subject's participation in the research, whether or not it is considered related to the subject's participation in the research.

Adverse events encompass clinical, physical and psychological harms. Adverse events occur most commonly in the context of biomedical research, although on occasion, they can occur in the context of social and behavioral research. Adverse events may be expected or unexpected.

Acute Adverse Events

Adverse events occurring in the time period from the delivery of radiation, through 90 days post treatment will be considered acute adverse events. *Adverse events will only be captured from medical oncology, radiation oncology, and surgical oncology clinic notes.*

***A dose- limiting toxicity (DLT) is a grade 3 toxicity deemed definitely related to treatment in the following categories: skin, rib bone (fracture), pulmonary (radiation pneumonitis), or neurological (intercostal or brachial plexus nerves) or any grade 4 or 5 toxicity deemed definitely attributed to the therapy.***

The following acute (<90 days) and late (>90 days – 36 months) toxicities definitely related to protocol treatment, as defined in CTCAE v5.0 will be reported

Grade 4 or higher toxicity in the below categories:

- Rib fracture
- Skin
- Radiation pneumonitis
- Neurologic
- Fat necrosis

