## 4.2 Toxicities and Dosing Delays/Dose Modifications

Any subject who receives treatment on this protocol will be evaluable for toxicity. Each patient will be assessed for the development of toxicity according to the Time and Events table in Section 5.4. Toxicity will be assessed according to the NCI Common Toxicity Criteria for Adverse Events (CTCAE), version 5.0. Dose adjustments should be made according to the system showing the greatest degree of toxicity.

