## 4.3 Concomitant Medications/Treatments

### 4.3.1 Systemic and Adjuvant Surgery

#### Systemic Therapy

Use of endocrine therapy after pre-operative radiation should be started within 21 days after pre-operative radiation, but it is encouraged to start the day after the post-radiation biopsy. Typically, for estrogen/progesterone positive patients, many will start endocrine therapy as they are waiting for surgery. Oncotype or Mammprint studies should be done on the biopsy specimen, if possible, prior to delivery of radiation if there is adequate tissue. If not, patient may require another biopsy to obtain this tissue and this will be at the discretion of the medical oncologist.

Surgery: Surgery can be done anytime from 8 to 52 weeks at the discretion of the surgeon. Sentinel lymph node biopsy can be done at time of lumpectomy or if patient prefers mastectomy.

Sentinel lymph node mapping: in the previous University of Maryland pre-operative study there were no instances of failed sentinel lymph node mapping on the 25 patients treated on the trial. Based on this experience, we have no reason to think that there should be an increase in failed mappings with the pre-operative radiation treatment. A peri-tumoral, intra-dermal or peri-areolar injection are allowed based on the discretion of the breast surgeon.

Sentinel lymph node mapping exclusions: In the elderly population (defined differently in by different trials and also based on medical comorbidities), a sentinel lymph node procedure is often not performed on low-risk patients. In this trial, we will not require women 70+ to have a sentinel lymph node mapping if it is deemed unnecessary by their treatment team. This must be documented in the patient's medical record.

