**5.2.5 3 months after Radiation**

Toxicity/Adverse event evaluation (via phone call by study team member)

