| Performance Status                                | X               |                          |                                |                 |                                    |                                 |                                 |                                 |                                  |                                  |
| Pregnancy Test                                    | X               |                          |                                |                 |                                    |                                 |                                 |                                 |                                  |                                  |
| Baseline AE Evaluation                            | X               |                          |                                |                 |                                    |                                 |                                 |                                 |                                  |                                  |
| Toxicity/AE Evaluations (including DLT)           |                 |                          | X                              |                 |                                    | X                   | X                               | X                               | X                                | X                                |
| Breast Imaging (Mammogram/ US, and or Ultrasound) | X               |                          |                                |                 |                                    |                                 |                                 | X                               | X                                | X                                |
| Breast MRI                                        | X   |                          | X                  |                 |                                    |                                 |                                 |                                 |                                  |                                  |

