4 Baseline MRI or contrast enhanced digital mammography(CEDM) is required, Post-radiation MRI is optional but highly recommended and if done, post radiation MRI must be completed at least four weeks after XRT and before surgery.

5 Completed via phone evaluation by study team member

6 Optional tumor sample collection can be done within +2 days of time point above

7 Archival or diagnostic tumor samples

8 Optional tumor sample to be completed within 30 days prior to radiation

9 Should be taken prior to radiation therapy

10 Patient and Physician cosmesis can be completed any time after consent but prior to radiation treatment

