#### Phase I Waiting Periods

Dose escalation on the phase I portion of this study should not occur until a sufficient waiting period has occurred after patients have been treated. A period of 90 days must pass in order to assess toxicity. If 90 days have transpired without DLT in each of the first seven (7) patients enrolled to a specific dose level, then dose escalation to the next level may proceed. Patients will continue to be enrolled to each dose level (up to a maximum of 15 patients) with ongoing assessment of those reaching 90 day follow-up so long as either criteria for defining the MTD or criteria for further dose escalation is not reached. If fifteen patients are enrolled to a given dose level yet criteria for adequate follow-up are not reached in a representative sample of patients, further enrollment to the protocol will be suspended until adequate follow-up is reached.

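### The acute-period source rule for adverse events, read literally, excludes the month-3 phone evaluation, which is the last scheduled DLT check serving the 90-day window

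*Protocol*

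**What the plan says.** Section 7.2.1 defines acute adverse events as those from radiation to day 90 and then limits their source: "Adverse events will only be captured from medical oncology, radiation oncology, and surgical oncology clinic notes". The same sentence is repeated for the late period.

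Other sections describe how toxicity is looked for:

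- Section 4.2: "Each patient will be assessed for the development of toxicity according to the Time and Events table in Section 5.4".
- Section 5.4, the row headed "Toxicity/AE Evaluations (including DLT"), is marked at month 3 with a footnote: "Completed via phone evaluation by study team member".
- Section 5.2.5 lists a single item for month 3: "Toxicity/Adverse event evaluation (via phone call by study team member"). No history, physical or breast examination is listed there.
- Section 5.4, footnote 1, covers the month-1, month-3 and month-6 contacts: "Follow-ups can be done within +/- 21 days of time points above and can be done via telehealth".
- Section 10.1, under waiting periods: "A period of 90 days must pass in order to assess toxicity".

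**The concern.** One instruction requires a phone evaluation for DLT. Another, taken at its word, does not accept a phone evaluation as a source of adverse events. The two meet at the primary endpoint, because DLTs within 90 days decide whether the dose goes up. If a coordinator applied Section 7.2.1 as written, an event first reported on the month-3 call would not enter the count unless one of the three services also wrote it down.

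Verification of DLTs by the study chair and the monitoring committee (Sections 2.4 and 10.1) does not repair this. It acts on DLTs that have been reported, so it can reject an event but cannot recover one that was never captured.

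**Working it through.** The protocol states no figure for this point, so there is none to reproduce. The check compares the text, then works out timing and direction.

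**1. Does any text reconcile the two instructions?** Sections 4.2, 5.2.5 and 5.4 make the call a required toxicity and DLT evaluation. Section 7.2.1 admits only clinic notes of three named services. No section says that the call is written up as such a note, and none exempts it. Section 7.2 adds that events are assessed at scheduled times and that events from consent to the end of the acute period are documented. This supports counting the call but does not lift the restriction.

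**2. How much of the DLT window depends on the call?** Inputs are the visit months and the 21-day window of Section 5.4, the 90-day DLT period of Section 10.1 and the surgery timing of Section 4.3.1. Months are converted at about 30.4 days.

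| Contact | Nominal day | Allowed range |
|---|---|---|
| Month 1 | 30 | 30 − 21 = 9 to 30 + 21 = 51 |
| Month 3 (call) | 91 | 91 − 21 = 70 to 91 + 21 = 112 |
| Month 6 | 183 | earliest 183 − 21 = 162 |

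Without the call, month 1 is the only scheduled toxicity evaluation before day 90. The days of the window left after it are:

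- nominal: 90 − 30 = 60
- fewest: 90 − 51 = 39
- most: 90 − 9 = 81

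The next scheduled evaluation would be no earlier than day 162, which is 162 − 90 = 72 days after the window closes. Escalation may have been decided by then.

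Surgery does not reliably fill the gap: "Surgery can be done anytime from 8 to 52 weeks at the discretion of the surgeon". That is day 8 × 7 = 56 to day 52 × 7 = 364. A surgical oncology note before day 90 is therefore possible but not assured, and the table schedules no toxicity evaluation at surgery or one month after it.

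**3. Which way does an error go?** Every escalation condition in Section 10.1 is an upper limit on the DLT count (0 of 7, at most 2 of 9, at most 3 of 12, at most 4 of 15). Every condition for exceeding the MTD is a lower limit (at least 3 of 9, 4 of 12 or 5 of 15). Removing an event can only move the decision towards escalation. For example, 3 DLTs in 9 patients means that the MTD is exceeded, whereas with one of them uncaptured the count is 2 of 9 and the dose escalates.

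**4. Which DLTs are exposed?** Section 7.2.1 describes grade 4 as life-threatening and grade 5 as death, and both meet its criteria for a serious event. Section 7.3.1 sends serious events to the monitoring committee once the study team is aware of them, with no limit on source. What remains is mainly non-serious grade 3 skin, rib, lung or nerve toxicity first reported on the call.

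**The case against.** The strongest reply is that the study team is not outside the three services. Section 4.3.1 refers to a radiation oncology study team, and Section 11.3 runs registration through the Radiation Oncology research office. A call by a team member is thus most naturally a radiation oncology contact and may well be filed as such. Further, a grade 3 complaint made on the call would ordinarily lead to an examination and an oncology note. Section 7.1.1 asks that patients with symptoms of pneumonitis be evaluated promptly and that a radiation oncologist take part. Staff are also unlikely to discard an evaluation that the schedule labels as covering DLT.

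Much of this stands, and it is why the effect is probably small. It does not remove the conflict, because it relies on sensible practice that the protocol does not state.

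Three stronger readings are tempting and are not supported:

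- *That escalation probabilities are materially inflated.* At a true DLT rate of 33%, the rule (0 of 7, otherwise at most 2 of 9) escalates with probability 38.5% under full capture. It would be 47.1% if 90% of DLTs were captured and 56.1% if 80% were. Those capture rates are assumptions with no basis in the protocol. They also thin all DLTs alike, although grade 4 and 5 events have another route.
- *That 60 of the 90 days go unobserved.* The call is scheduled. The 60 days show what depends on it, not what is lost.
- *That the late-period sentence and the exclusion of other records are equally at fault.* The month-6, 12, 24 and 36 evaluations each include a history and physical (Sections 5.2.6 to 5.2.9), and late events do not enter the 90-day rule. Limiting routine collection of non-serious, non-DLT events to the treating services appears deliberate. Clinic notes can also report imaging findings and events treated elsewhere.

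**Conclusion.** The concern holds in a narrow form. In the acute period, the source sentence conflicts on its face with the month-3 phone evaluation, and that evaluation is the last scheduled check serving the DLT window. The direction of any error is certain: towards escalation. Its size cannot be derived from the protocol. It depends on whether the call is filed as a radiation oncology note and on how often a non-serious grade 3 DLT is first reported there. With the serious-event route intact, the loss is probably small. The dose-escalation rule, its thresholds and the sample size are unaffected. The wording should be corrected because it governs primary-endpoint data and the correction costs almost nothing.

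**What to change.** In Section 7.2.1, acute period only, delete the word *only*, keep the three clinic-note sources, and extend the sentence with: *and from the month-3 study-team phone evaluation; any suspected DLT known to the study team from any source is also captured, graded and attributed.*

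The late-period sentence and the general restriction on non-serious, non-DLT events can stay as they are. The change is one amended sentence and slightly more review by existing coordinators, with no new visits or procedures.
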